# ULTIMATE-SHF trial (UdenafiL Therapy to Improve symptoMAtology, exercise Tolerance and hEmodynamics in patients with chronic systolic heart failure): study protocol for a randomized, placebo-controlled, double-blind trial

**DOI:** 10.1186/1745-6215-14-188

**Published:** 2013-06-22

**Keywords:** Phosphodiesterase type 5 inhibitor, Udenafil, Chronic heart failure, Exercise capacity

## Abstract

**Background:**

Over the last few years, the use of phosphodiesterase type 5 (PDE5) inhibitors has been expanded to management of various cardiovascular disorders beyond pulmonary arterial hypertension. This study is designed to investigate the ability of udenafil, a newly developed long-acting PDE5 inhibitor, to improve functional capacity and hemodynamic status in a cohort of chronic systolic heart failure (SHF) patients.

**Methods/design:**

Stable, chronic SHF patients will be randomly assigned to placebo (26 patients) or udenafil at a dose of 50 mg twice per day (26 patients) for the first 4 weeks followed by 100 mg twice daily for the next 8 weeks. Eligibility criteria will be age ≥18 years, clinical diagnosis of chronic SHF with current New York Heart Association class II to IV symptoms, left ventricular ejection fraction ≤ 40%, and experience of at least one of following during the 12 months prior to study entry: hospitalization for decompensated heart failure, acute treatment with intravenous loop diuretics or hemofiltration, or pulmonary artery systolic pressure ≥40mmHg on transthoracic echocardiography. Pharmacological therapy for SHF will be optimized in all patients at least 30 days before study entry. The primary outcome will be the change of maximal oxygen uptake, assessed by cardiopulmonary exercise testing. Secondary outcomes will include changes in ventilatory efficiency (minute ventilation/carbon dioxide production slope), left ventricular systolic and diastolic parameters, pulmonary artery systolic pressure, plasma concentration of brain natriuretic peptide, occurrence of mortality or hospitalization for heart failure, and the occurrence of any adverse event.

**Clinical trial registration:**

Unique identifier: NCT01646515

## Background

Heart failure is a leading cause of death that continues to cause a significant socioeconomic burden worldwide [1]. The prevalence of chronic heart failure (HF) in relation to left ventricular (LV) systolic dysfunction is estimated to be as high as 2 to 11% [2]. Despite the aggressive use of medications, such as angiotensin-converting enzyme inhibitors, β-blockers and spironolactone, proven to improve the survival of chronic HF patients with a reduced LV ejection fraction, mortality and morbidity remain high, and one of the potential reasons for this might be the development of pulmonary hypertension. According to a number of earlier works, up to 60% of patients with severe LV systolic dysfunction develop pulmonary hypertension [3,4]. Hence, it is conceivable that the development of pulmonary venous or mixed pulmonary venous/arterial hypertension, which results in HF symptoms such as dyspnea and limitation of exercise capacity, and consequently adversely affects quality of life and prognosis, is an important milestone in the progression of uncomplicated LV systolic dysfunction to clinically manifested HF. In this respect, development of a new therapeutic option that deals with the issue of pulmonary hypertension in association with LV systolic failure is both attractive and clinically relevant.

Phosphodiesterase type 5 (PDE5) is a key enzyme in the catabolism of cyclic guanine monophosphate (cGMP) and is predominantly abundant in the vascular smooth muscle cells of the pulmonary vasculature [5]. Given the important role of cGMP in the regulation of nitric oxide and that defective nitric oxide release is a major factor of vasoconstriction in chronic HF [6], the addition of PDE5 inhibitors to established medications for chronic HF could be a theoretically appealing treatment strategy. PDE5 inhibitors were initially introduced as a treatment option for erectile dysfunction, and even in the late 20th century this type of drug was believed to have little to contribute in the cardiology field. However, since PDE5 inhibitors were found to have beneficial effects on pulmonary arterial hypertension in man [7], and the confirmation of this finding in clinical trials [8,9], PDE5 inhibition is now considered a viable therapeutic option for the treatment of pulmonary arterial hypertension. In addition to their favorable therapeutic impacts on pulmonary arterial hypertension, PDE5 inhibitors have recently been shown to be effective therapeutics in patients with chronic systolic heart failure (SHF) [8,10].

Udenafil (Zydena®; Dong-A Pharmaceutical Company, Seoul, South Korea) is a newly developed long-acting PDE5 inhibitor [11,12], with efficacy and safety profiles comparable with those of other PDE5 inhibitors [13]. Udenafil is similar to sildenafil in molecular structures (Figure 1), and is comparable with sildenafil in terms of PDE5 selectivity and its broad range of safety margin [14]. Furthermore, laboratory data showed that udenafil inhibits ventricular hypertrophy and fibrosis in a rat HF model [15]. In the preclinical study, udenafil increased serum cGMP levels, decreased intracellular Ca^2+^ concentrations, and produced vasodilatation. In this proposed double-blind, randomized, placebo-controlled trial we hypothesize that udenafil will ameliorate symptoms, and improve exercise capacity and hemodynamic status in patients with chronic SHF (ULTIMATE-SHF trial; NCT01646515).

**Figure 1 F1:**
[figure not shown]
Chemical structure of udenafil.

## Methods/design

### Study population

The ULTIMATE-SHF trial is designed as a prospective, single-center, randomized, double-blind, placebo-controlled study targeting patients with chronic SHF, in whom optimal medical therapy has been established. Patients with stable chronic SHF that meet the prespecified eligibility criteria and provide written informed consent will be enrolled (Table 1). Detailed information on benefits and risks will be provided to study candidates. Pharmacological therapy for heart failure will be optimized in all patients at least 30 days before study entry.

**Table 1 T1:** Eligibility criteria

**Inclusion criteria**	**Exclusion criteria**
1. Able to provide written informed consent	1. FEV1 <80% of predicted value or FEV1/FVC <70% on spirometry at screening
2. Men and women ≥18 years old	2. Other valve diseases greater than mild stenosis and/or regurgitation
3. Established clinical diagnosis of chronic systolic heart failure with NYHA class II to IV symptoms currently	3. Neuromuscular, orthopedic, or other noncardiac conditions that prevent completion of a maximal exercise testing
4. Left ventricular ejection fraction ≤40%, as determined by echocardiography at the baseline echocardiographic examination	4. Infiltrative/ inflammatory myocardial or pericardial disease
	5. Primary pulmonary arteriopathy
5. Have experienced at least one of the following criteria in the 12 months before study entry:	6. Current use of nitrate preparation therapy (will be deleted) or other PDE5 inhibitors (that is, sildenafil, vardenafil, tadalafil) or cytochrome P450 3A4 inhibitors (ketoconazole, itraconazole, erythromycin)
- Hospitalization for decompensated heart failure	
- Acute treatment with intravenous loop diuretics or hemofiltration	7. Severe hypotension (SBP <90 mmHg or DBP <50 mmHg) or uncontrolled hypertension (SBP >180 mmHg or DBP >100 mmHg)
- Pulmonary artery systolic pressure ≥40 mmHg by echocardiography	8. Noncardiac illness with estimated life expectancy <1 year at the time of study entry, based on the judgment of the attending physician
6. Stable medical therapy for 1 month before study entry – no addition or removal or change in major class of medication dosage; that is, renin–angiotensin–aldosterone inhibitors, β-blockers	9. Known severe renal dysfunction (GFR <30 ml/minute/1.73 m^2^ by MDRD equation)
	10. Known severe liver disease (ALT or AST level >3 times the upper normal limit, alkaline phosphatase or total bilirubin >2 times the upper normal limit)
	11. Actively involved in any physical training program for at least 6 months before study entry
	12. Listed for heart transplantation

*ALT*, alanine aminotransferase; *AST*, aspartate aminotransferase; *DBP*, diastolic blood pressure; *FEV1*, forced expiratory volume in 1 second; *FVC*, forced vital capacity; *GFR*, glomerular filtration rate; *MDRD*, Modification of Diet in Renal Disease; *NYHA*, New York Heart Association; *SBP*, systolic blood pressure.

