### Study design and medications

Patient screening for trial eligibility will be based on reviews of medical records and echocardiographic results before baseline visits. After confirming study eligibility, baseline examinations (see the next section) will be conducted. Subsequently, patients will be randomized in a double-blind fashion to receive either udenafil or placebo (1:1) on top of any background therapeutic regimen in compliance with current recommendations [16], utilizing the randomization scheme depicted in Figure 2. An independent computer-generated list of random number will be used for participant allocations. Patients will receive either 50 mg udenafil or placebo twice daily for the first 4 weeks, and then if tolerated the dosage will be doubled to 100 mg twice daily for the next 8 weeks. Placebo and active study drugs (that is, udenafil) will appear to be identical and will be provided in blinded kits.

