**Figure 2 F2:**
[figure not shown]
**Study visit schedule of the ULTIMATE-SHF trial.** bid, twice daily; CPET, cardiopulmonary exercise test; Echo, echocardiography; Exercise Echo, exercise echocardiography; NYHA, New York Heart Association.

In the phase I trial, 42 healthy male volunteers received 25 to 300 mg of udenafil per day and experienced only minor adverse events [17]. Furthermore, a clinical trial on erectile dysfunction showed that 100 to 200 mg udenafil was well tolerated [18]. Because the half-life of udenafil is 7 to 9 hours, which is longer than that of sildenafil (4 hours), the study drug will be provided twice daily. Throughout the trial, medications prescribed by referring physicians will not be changed.

The ULTIMATE-SHF trial has been approved by the Clinical Research Institute at our hospital (H-1102-063-352), and the study drug, udenafil, has been approved as Investigational New Drug for therapeutic use in patients with chronic SHF, by the Korean Food and Drug Association.

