### Safety

Any participants with a hypersensitivity reaction to the study drug or an adverse event after study medication, those that do not want to remain in the trial, or those that comply with medication <80% will be dropped from the trial, as will those judged to be at risk due to participation in the trial by an attending physician.

Udenafil has been reported to be safe and well tolerated by healthy volunteers [17], and by patients with erectile dysfunction [14]. No serious adverse events occurred in either study. Common adverse events included nausea, headache, facial flushing, febrile sensation, penile erection, and eyeball pain, all of which have been reported to adverse events of other PDE5 inhibitors. Adverse events will be immediately reported directly to the study investigators, and study staffs will be obligated to manage these events. Patients will be interviewed at each visit about the occurrence of any adverse events, and onset time, duration, and severity will be recorded on case report forms. The possibility of causal relationships between the study drug and the intensities of adverse events will be evaluated by the investigators. The investigators are mandated to report serious adverse events to the institutional review board within 24 hours of recognition. A data and safety monitoring committee will monitor the safety of patients participating in the trial and all ongoing serious adverse events will be closely followed until these conditions have stabilized.

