### Study withdrawals

Patients will be permitted to request withdrawal from treatment at any time without providing reasons. The primary investigator and the attending physician will also have authority to drop patients from the trial treatment if it is considered that further participation in the trial would be detrimental to the patient's well-being. Such treatment withdrawals will be documented using a case report form and in patient's medical records. In addition, we have a plan to evaluate the results of this trial in the middle of this study, and based on these interim results the trial can be prematurely terminated if the drug effect would be highly suggested to be beneficial or harmful.

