## Trial status

Patient recruitment.

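### Exclusion 6 in Table 1 lists current nitrate use as a bar to entry and, in the same line, marks it for deletion without a reason or a replacement safeguard

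*Protocol article*

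**What the plan says.** Table 1 (Study population) gives exclusion 6 as "Current use of nitrate preparation therapy (will be deleted) or other PDE5 inhibitors", and then names cytochrome P450 3A4 inhibitors as well. The text above the table ties enrolment to these criteria: "Patients with stable chronic SHF that meet the prespecified eligibility criteria and provide written informed consent will be enrolled". The Trial status section reads "Patient recruitment".

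On concomitant treatment, the section Study design and medications has study drug given "on top of any background therapeutic regimen in compliance with current recommendations". Later in the same section, after Figure 2, it adds: "Throughout the trial, medications prescribed by referring physicians will not be changed".

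On pharmacology, the Background section links cGMP to the regulation of nitric oxide and reports that, in preclinical work, "udenafil increased serum cGMP levels, decreased intracellular Ca^2+^ concentrations, and produced vasodilatation".

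**The concern.** An exclusion criterion has to tell the person screening a patient whether that patient may enter. This one gives two signals: current nitrate use excludes, and that exclusion is to go. The note does not say exactly what is to be removed, when, on whose authority or why.

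The criterion bears on safety. The article describes the study drug as a vasodilator acting through cGMP, and exclusion 6 puts nitrates beside other PDE5 inhibitors as co-medication that bars entry. Removing that bar would be a change of substance, and the article offers no argument for it and no protection in its place.

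**Working it through.** The point rests on wording, so there is nothing to compute. The check sets the relevant statements side by side.

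1. **Status of the note.** It stands directly after the nitrate item and before the PDE5 inhibitor item, and the sentence continues normally after it. It is running text in a current criterion, not an amendment log, a redaction or a broken table cell. Its natural referent is the nitrate item alone.

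2. **Possible readings.**
   - (a) The exclusion is in force and the note is left over from drafting.
   - (b) The exclusion is to be dropped and nitrate users may then enter.
   - (c) Nitrates are to be withdrawn from the patient before entry. This is hard to square with "Throughout the trial, medications prescribed by referring physicians will not be changed", and no washout is described anywhere.

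   Readings (a) and (b) lead to opposite decisions for the same patient.

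3. **Does another section decide between them?**
   - The eligibility summary in the Abstract gives no exclusions.
   - Inclusion 6 (stable therapy for one month) names renin–angiotensin–aldosterone inhibitors and β-blockers, not nitrates.
   - Study design and medications, Follow-up protocol, Safety, Study withdrawals and the Discussion do not mention nitrates.

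   Exclusion 6 is therefore the only statement on the subject.

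4. **What would remain under reading (b)?** The other protections are general, and none names nitrates:

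| Safeguard | Section | When it can act |
|---|---|---|
| Systolic pressure below 90 or diastolic below 50 mmHg excludes | Table 1, exclusion 7 | At entry, on pressure before study drug |
| Dose doubled at 4 weeks only if tolerated | Study design and medications | After exposure |
| Dropped after an adverse event; safety committee monitoring | Safety | After exposure |
| Physician may drop "those judged to be at risk due to participation in the trial by an attending physician" | Safety | Any time, by judgment |
| "The primary investigator and the attending physician will also have authority to drop patients from the trial treatment" | Study withdrawals | During treatment, by judgment |

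   Physician judgment can act before an event occurs, but it is not a fixed entry rule. The blood-pressure limit screens for hypotension that is already present, not for co-medication.

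5. **How far does the article document the hazard?** It describes vasodilatation with udenafil alone, from preclinical work, and it treats nitrate use as a reason for exclusion. It reports no data on the combination. That supports calling the criterion safety-relevant, but not putting a size on the risk.

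**The case against.** The strongest reply is that a note about a future deletion leaves the present rule in force. As printed, nitrate users are excluded. If the note is an editing remnant, the trial has no design fault, only an untidy table. Much of this stands: the exclusion does hold as printed, and the remnant reading is plausible. It does not remove the need for correction, because the article gives no way to tell which reading is right, and carrying out the note as written would lift a safety exclusion.

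A reader might infer three stronger things, none of which the article supports.

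- **That the trial is recruiting under an open entry rule.** The article condenses a fuller protocol that is not shown. It states that the hospital's research institute approved the trial. The status line shows that recruitment is the current stage, but not that staff screen from this table or that the approved rule is unsettled.
- **That the treatment section positively permits nitrates.** The phrase "on top of any background therapeutic regimen in compliance with current recommendations" refers to recommendations that are not reproduced, and it concerns patients already found eligible. It neither bars nor allows nitrates. What can be said is narrower: without exclusion 6, nothing in the article would bar them.
- **That power is at risk.** Any such figure would need an assumed share of nitrate users and an assumption that they are lost to analysis. The article gives neither, so none is offered.

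A last objection is that keeping the exclusion prejudges the answer, since a deletion may already have been approved. That is fair, and it is why the fix includes a check against the approved protocol.

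**Conclusion.** The point holds as a self-contradiction in a printed, safety-relevant entry criterion. The exclusion is in force on the page, its removal is announced on the same line, and no other section resolves the conflict or justifies the removal.

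Its size is one criterion, which applies to each of the 52 planned patients (26 per group). Any harm to patients is conditional on the note being carried out, and the note may be only a drafting leftover. The conclusion rests on the article alone and makes no claim about the wording of the full protocol, the number of nitrate users, the risk of an event, the sample size or power. It should be fixed, because the ambiguity is easy to remove and the cautious reading is the one already printed.

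**What to change.** Delete the bracketed three-word note and keep current nitrate use as an exclusion. Confirm that this matches the approved protocol. Check the medication records already held for any enrolled patient taking nitrates: medical records are reviewed at screening, and medication changes are collected at every visit. If the investigators do intend to admit nitrate users, do so only through an approved amendment that gives a safety justification.

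The cost is a one-line edit, one comparison with the approved protocol and one review of existing records. If the exclusion has been applied as printed, no patient is affected. If nitrate users were enrolled, each would need review and a few might stop treatment. They should still be asked to have the 12-week exercise test, because the principal analysis is by intention to treat.

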### Study design and medications

Patient screening for trial eligibility will be based on reviews of medical records and echocardiographic results before baseline visits. After confirming study eligibility, baseline examinations (see the next section) will be conducted. Subsequently, patients will be randomized in a double-blind fashion to receive either udenafil or placebo (1:1) on top of any background therapeutic regimen in compliance with current recommendations [16], utilizing the randomization scheme depicted in Figure 2. An independent computer-generated list of random number will be used for participant allocations. Patients will receive either 50 mg udenafil or placebo twice daily for the first 4 weeks, and then if tolerated the dosage will be doubled to 100 mg twice daily for the next 8 weeks. Placebo and active study drugs (that is, udenafil) will appear to be identical and will be provided in blinded kits.

**Figure 2 F2:**
[figure not shown]
**Study visit schedule of the ULTIMATE-SHF trial.** bid, twice daily; CPET, cardiopulmonary exercise test; Echo, echocardiography; Exercise Echo, exercise echocardiography; NYHA, New York Heart Association.

In the phase I trial, 42 healthy male volunteers received 25 to 300 mg of udenafil per day and experienced only minor adverse events [17]. Furthermore, a clinical trial on erectile dysfunction showed that 100 to 200 mg udenafil was well tolerated [18]. Because the half-life of udenafil is 7 to 9 hours, which is longer than that of sildenafil (4 hours), the study drug will be provided twice daily. Throughout the trial, medications prescribed by referring physicians will not be changed.

The ULTIMATE-SHF trial has been approved by the Clinical Research Institute at our hospital (H-1102-063-352), and the study drug, udenafil, has been approved as Investigational New Drug for therapeutic use in patients with chronic SHF, by the Korean Food and Drug Association.

### Blinding

Study patients, interviewers responsible for administering questionnaires, inspectors that conducted echocardiography and cardiopulmonary exercise tests (CPETs), and the study investigators and directors will be blinded from details of the randomization. Unblinding will be only accepted by the independent data and safety monitoring committee when a serious adverse event occurs, upon request from regulatory authorities, or when information regarding the allocation procedure is deemed important from the perspective of patient safety.

### Follow-up protocol

The trial duration is expected to be 3 months. Participants will attend study visits at screening, baseline, and weeks 4 and 12. At each visit, patients will undergo a complete physical examination, medical history-taking, and an assessment of drug compliance. Investigators will evaluate all clinical and laboratory adverse events at each visit. New York Heart Association functional class and predefined clinical events as described below will be recorded at each clinical visit. Venous blood will be drawn after a 15-minute rest period at screening, and at 4-week and 12-week visits, and will be subjected to the following test battery: B-type natriuretic peptide, complete blood count, electrolyte panel, serum creatinine, and liver function test. At screening visits, echocardiography will be performed at rest, and based on the results obtained study investigators will decide on patient eligibility. At baseline and at 12 weeks, participants will undergo CPET (V_Max_ 229 Respiratory Analyzer; SensorMedics, Homestead, FL, USA) and exercise echocardiography to evaluate exercise capacity in a quantitative manner. At all study visits, researchers will collect health-related information, such as adverse events, admission for acute decompensated HF, and change in medication. In addition, medication compliance of all participants will be carefully assessed by the pill-count method at every visit.

